**Fig. 3 Fig3:**
[figure not shown]
Life coaching flow chart

#### Data collection

Peer researchers will administer surveys for part one of the study, the observation of SEWB, and a final qualitative interview for part two to understand the experience of life coaching. Life coaches will regularly capture data about a tenant’s progress toward their goals for part two. The data collection methods are explained in more detail in the following sections and summarised in Fig. 4.

**Fig. 4 Fig4:**
[figure not shown]
Data collection schema

#### Survey

The MTAL survey, including items examining SEWB, was initially developed and used as part of an Indigenous led First 1000 days Australia initiative to describe the aspirations and needs of Aboriginal and Torres Strait Islander families [31]. The survey was modified to meet the needs of the MTAL project and piloted by an Aboriginal controlled health and community service in the eastern region of Melbourne with 22 local community members. The survey was then tailored to the AHV context by AHV staff and researchers to reflect the shift in focus from parenting to people who are tenants of AHV. The revised survey was piloted with five Aboriginal and Torres Strait Islander AHV staff. In addition to demographic information (age, Aboriginal and Torres Strait Islander identification, relationship status, postcode) the survey consists of 12 domains as outlined in Table 1.

**Table 1 Tab1:** Data collection

Data Type	Domain	Key measures
Survey	Education, Employment & Finances	Highest level of education completed, employment status, barriers to employment, spending, bill payments, bill stress
	Family	Number of children birthed/adopted/cared for, dependents/age/relationship**,** Strengths-based parenting tool [32]
	Out of Home Care	Removals/child protection services, age of housing independence, cultural placement plan
	Culture and Community	Connection to culture and community, community attitudes
	Cultural safety	Unfair treatment, unsafe environments
	Service Use	Service use and availability
	Self determination	Choice and control in decision making on issues
	Health	Health Conditions, Euroqual 5D -5 L [33], disability, smoking
	Wellbeing	Kessler-5 [34], Mental Health Continuum [35], Aboriginal Resilience and Recovery Questionnaire [9]
	Housing	Number and type of occupants, household amenities, financial stress due to tenancy
	Family violence	Experience of controlling, unsafe or threatening behaviour [36]
	Goal setting questions	Key categories of goals/aspirations
Pulse Check	Strengths	Key strengths used
	Resources	Use of community resources
	Resilience	Self-efficacy questions from Aboriginal Resilience and Recovery Questionnaire [9] and help seeking question
	Life coaching	Description of experience and impact of life coaching
Support Plan	Goals and actions	Number and type of goal/s, number of action/s, goals and actions achieved/partially achieved/not achieved
Interview	Life coaching	Experience and impact of life coaching
	Strengths	Awareness and use of strengths
	SEWB	Impact of life coaching on SEWB
Administrative Data	Demographic	Age, Gender
	Household	Household make up (adults-no children, elder, young family with preschoolers, older family with school age children) and household type (unit/house)
	Rent	Rent in arrears (Yes/No)
	Complaints	Number of complaints against household

Survey items are based on either established instruments, modified instruments or instruments developed by researchers or through consultation with key stakeholders. The Aboriginal Resilience and Recovery Questionnaire has been developed and validated for use in the Victorian Aboriginal and Torres Strait Islander population [9].

Surveys will be offered to tenants by peer researchers at baseline, 6 and 18 months. At the completion of the survey all participants are given a debriefing statement containing information about services that could offer support if the questions in the survey have caused them any distress. Some participants may be vulnerable to distress due to potential underlying mental health and/or SEWB vulnerabilities, such as experiences of complex or intergenerational trauma [37]. Survey data will be collected using the Qualtrics platform on a tablet and exported for analysis.

#### Support plan and pulse checks

Each life coach will document information about goal category, actions to achieve goals, goal status and goal attainment date in a support plan. Support plan data will be collected on an AHV database and a report extracted and supplied to the researchers for analysis.

A pulse check has been developed by researchers with AHV staff to determine progress with life coaching and will be administered by life coaches every 3 months. The pulse check is a short survey of mainly multiple-choice questions examining strengths and services used to progress towards goals and ratings of self-efficacy and help seeking behaviour. Open ended questions prompt the participant to reflect on their learning and experience of life coaching to date. Pulse check data will be collected via a Qualtrics survey administered by life coaches via a tablet.

#### Interview

At the time of the 18-month survey, peer researchers will invite all life coaching participants to participate in a semi structured interview. The qualitative interview, based on the principles of appreciative inquiry [38], will explore the participants experience of life coaching. Questions are outlined in an interview schedule and will address participant reflections on their experience of life coaching, strengths, skills and resources used, and the impact of life coaching on their life. Data from the semi structured interview will be audio recorded and transcribed.

#### Administrative data

Administrative data will be analysed on all AHV tenants in the three regions to enable comparisons to be made between the AHV tenant population, survey and life coaching participants. AHV routinely collects administrative data for operational purposes as the landlord. Administrative data will include age, gender, household make up, household type. Administrative data on rent in arrears, tenant related maintenance charges and complaints will also be collected as an absence of issues in relation to this data is indicative that tenants are experiencing fewer of the difficulties in life that may have led to these.

#### Data linkage and protection

Data linkage across administration, survey and life coaching data collection tools will occur through an AHV unique tenant identifier. Date of birth and address will also be collected for the survey to enable identity confirmation checks should the peer researcher enter the incorrect unique tenant identifier number.

Data collected for the support plan as part of AHV providing a life coaching service will be stored by AHV as part of their normal client management database. Survey data will be securely stored by the university-based research team along with life coaching pulse check data. Audio recorded qualitative interview data will be identified according to unique identifier and will be collected by peer researchers and submitted to the university researcher for secure storage. Administrative data will be provided to university research team identified only by unique identifier. Data identified by unique identifier, and for the survey also by date of birth and address, will be kept in password protected databases. Access will be restricted to researchers undertaking the analysis.

### Culturally safe and ethical evaluation

The MTAL study aligns with contemporary principles and guidelines of research with Aboriginal and Torres Strait Islander peoples. MTAL follows the lead of Aboriginal and Torres Strait Islander community members and organisations who identified the need to build the evidence base for strength-based interventions. In this way the study respects and acknowledges the rights of Aboriginal and Torres Strait Islander people to design, plan, implement and evaluate their own programs [39, 40]. The survey reflects and captures Aboriginal and Torres Strait Islander knowledge of health and wellbeing [41]. The structure of the study in engaging Aboriginal and Torres Strait Islander peer researchers and life coaches builds the capacity of local people in the three communities to undertake research and evaluation and develop valuable work experience [40]. The processes, intervention models and data generated in the study will be available to be used for the benefit of AHV and other organisations to promote strengths-based initiatives and advocate for funding. The study incorporates periodic opportunities to share evaluation findings and be accountable to local communities of interest [39].

A number of strategies have been developed to minimise the risk of participants being adversely affected by their involvement in the project. A debriefing statement, as previously described, will be provided to participants after survey administration including information about support services. A distress protocol, which includes processes to temporarily or permanently cease the activity, will be implemented should participants exhibit any distress during the survey, life coaching or interview. Participants will be offered a $40 voucher for their time in completing surveys and a $60 voucher for completing both the 18-month survey and interview.

### Statistical analysis

#### Representativeness of study participants

The data analysis will initially involve comparisons to determine the representativeness of the study participants. The first comparison involves examining whether the participants in the initial survey are representative both of all tenants in each of the three regions and of the full tenant population of AHV. AHV administrative data items will be compared for survey and non-survey participants. This comparison will guide the extent to which study findings could be generalised to the population of AHV tenants or tenants in other settings.

The second comparison examines the comparability between participants in the life coaching program and survey participants who declined life coaching. Comprehensive survey data will be used to explore differences between these two groups that could influence outcomes and potentially confound the estimated difference in outcomes between life coaching participants and those who declined. Potential confounders specified a priori will include education level, life stage, employment status, financial stress, family violence, childhood removal from natural family, out of home care, health and wellbeing, housing stability (e.g. absence of rent in arrears) and connection to community and family.

All comparisons will be made using linear and logistic regression for continuous and binary outcomes respectively. Robust estimation will be used to account for the clustering structure within the study, according to similarity (non-independence) of outcomes between people within a region and similarity of outcomes between people receiving life coaching from the same life coach.

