### Study population

This study is conducted in partnership with AHV, which is an Aboriginal community organisation responsible for managing over 1500 rental properties for Aboriginal and Torres Strait Islander people living in Victoria, Australia. AHV has identified three regions in which the study will be conducted: North west metropolitan Melbourne and two regional areas; Ballarat and the greater Geelong area. The regions were selected by AHV based on data that indicated that the population of tenants in the regions experienced more stability in managing tenancies (e.g. fewer issues with rental payments) and may be more able to participate in life coaching. All Aboriginal and Torres Strait Islander people aged 16 years and over, who are tenants of AHV and reside in the three regions are eligible to participate. There will be three main groups of people in the research, those who decline to be surveyed, survey participants (Part 1 sample), and a subset of survey participants who become life coaching participants (Part 2 sample) as shown in Fig. 1.

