**Fig. 1 Fig1:**
[figure not shown]
Participants type and anticipated numbers

Based on the uptake in the pilot survey, of the 389 tenant holders we approach in the three regions, we are anticipating that a minimum of 51% will agree to the survey. We are expecting 146 of the 200 tenant holders surveyed (73%) to continue on to life coaching. There may be additional tenants in each household recruited to the life coaching and/or survey.

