#### Outcome comparisons and SEWB over the period of life coaching

The final comparison compares the SEWB of life coaching participants with non-participants. The assessment of outcomes will be made by analysing a range of outcome variables reflecting the holistic nature of SEWB as defined earlier. Several aspects of the program delivery are hypothesised to bring about changes in the SEWB of life coaching participants. These include the total hours spent in life coaching, the period of life coaching, the number of and degree to which participants achieve goals and their related actions. It is anticipated that the type of goal chosen will influence which outcomes variable may change. For example, a goal to improve financial resources would likely result in a reduction in financial stress and perhaps an improvement in wellbeing but may have less impact on other outcomes such as connection to culture.

The predictor and outcome variables of interest are shown in Table 2.

**Table 2 Tab2:** Predictor and outcome variables

Predictor variables	Outcome variables
Period of life coaching (months)	Employment status
Exposure/dose of life coaching (hours)	Financial stress
Type of goal (category e.g., financial, employment)	Strengths based parenting
Number of goals (not achieved/partially achieved /achieved)	Connection to culture
Number of actions (not achieved/partially achieved/achieved)	Service use
	Health
	Wellbeing - resilience, psychological distress and mental health

Given the non-randomised design, adjusted analyses will be conducted to delineate whether any observed differential outcomes are due to coaching or could be accounted for by initial differences between the people who chose or declined to participate in life coaching. Comparisons will be adjusted for confounders specified a priori (as above) as well as baseline measure corresponding to the outcome under consideration.

For outcomes measured on a continuum (Euroqual 5D-5L, Kessler-5, Mental Health Continuum, and Aboriginal Resilience and Recovery Questionnaire) multilevel growth models [42] will be used to examine within-person change over time within individuals and communities in each region. The models will be extended to examine the effects of family contexts on the growth curves including individual, family and community level social determinants as measured in the surveys.

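### Three regions are too few for the robust (cluster-adjusted) standard errors that the protocol assigns to region in its linear and logistic comparisons

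*Protocol article*

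**What the plan says.** All statements are in the protocol article.

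- **Regression method** (Statistical analysis, Representativeness of study participants): "All comparisons will be made using linear and logistic regression for continuous and binary outcomes respectively".
- **Clustering** (same paragraph): "Robust estimation will be used to account for the clustering structure within the study". The two sources named are "similarity (non-independence) of outcomes between people within a region and similarity of outcomes between people receiving life coaching from the same life coach".
- **Number of regions** (Study population): "AHV has identified three regions in which the study will be conducted", one metropolitan and two regional.
- **Continuous scales** (Outcome comparisons and SEWB over the period of life coaching): for EQ-5D-5L, Kessler-5, Mental Health Continuum and the resilience questionnaire, "multilevel growth models [42] will be used to examine within-person change over time within individuals and communities in each region".
- **Numbers** (text under Fig. 1): "of the 389 tenant holders we approach in the three regions, we are anticipating that a minimum of 51% will agree to the survey". Of 200 surveyed, 146 (73%) are expected to take up coaching.

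The article gives no small-sample correction, reference distribution, significance level or fixed effect for region.

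**The concern.** A cluster-robust variance is estimated from the spread of one score total per cluster. Its justification is a large number of independent clusters; the number of people inside them does not help. With three regions the variance rests on about two independent pieces of information. It is therefore very noisy, and small values of the standard error produce large test statistics by chance.

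The result most exposed is coached versus declined. The outcome section calls this the final comparison and gives no other method for outcomes that are not among the four named scales. In Table 2 these include employment status, financial stress, strengths-based parenting, connection to culture and service use. The Discussion says that results will be used to advocate with funders, so false positives well above the conventional rate would matter.

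**Working it through.** **Inputs from the article.** Three regions; 389 approached; 51% agreeing; 200 surveyed; 73% coached.

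**Assumptions, because the article gives no figures.** Two-sided 5% level; region ICC 0, 0.02 or 0.05; region sizes from 67/67/66 to 140/35/25; a sandwich variance clustered on region, which is the natural reading of robust estimation that accounts for clustering.

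**1. The article's own counts.** 389 × 0.51 = 198.4, in line with the stated 200. 200 × 0.73 = 146, as stated, which leaves 200 − 146 = 54 not coached.

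**2. Type I error, analytic.** With G = 3 equal regions and the factor G/(G−1), the statistic is approximately t with G − 1 = 2 df. For 2 df, P(|t| > c) = 1 − c/√(2 + c²).

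- With c = 1.96: 1 − 1.96/√(2 + 3.8416) = 1 − 1.96/2.4169 = 0.189.
- Without the finite-sample factor, c = 1.96 × √(2/3) = 1.600: 1 − 1.600/√(2 + 2.561) = 0.251.

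**3. Type I error, simulated.** N = 200, 73% coached, no coaching effect, linear model, 3,000 trials per setting, 0 or 10 covariates.

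| Setting | Factor included, 1.96 | Factor included, t(2) | No factor, 1.96 |
|---|---|---|---|
| Equal regions | 18-20% | 5-6% | 25-27% |
| Unequal regions | 21-27% | 5.5-8% | 29-34% |
| Unequal regions, uptake also differs by region | 26-28% | 7-10% | 35-37% |

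The ICC hardly changes these figures. Adding region indicators while still clustering the variance on region does not help either: those runs gave 18-28% against 1.96. The remedy must therefore remove region from the clustering as well as add the indicators.

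**4. Price of the t(2) reference.** The critical value is 4.303, so intervals are 4.303/1.96 = 2.2 times as wide for the same standard error. For power, take an assumed effect of 0.45 SD:

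- SE = √(1/146 + 1/54) = 0.159 SD, and 0.45/0.159 = 2.83.
- Normal-based power with a well-estimated SE: Φ(2.83 − 1.96) ≈ 0.81.
- Noncentral t on 2 df, cut-off 4.303: about 0.36.

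A simulation check (4,000 trials per setting, sizes from 67/67/66 to 130/35/35) gave 35-45% power with t(2), against 78-83% with region as a fixed effect and a model-based SE.

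**5. Region as a fixed effect, model-based SE.** Simulated type I error was 4.6-6.1%. This assumes no coach clustering and the same coaching effect in every region.

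**6. Coach level.** With region fixed effects, clustering on coach (3 to 6 coaches assumed, coach ICC 0 to 0.05) gave 7-21% against 1.96. The worst case was one coach per region with coach ICC 0.05. Few coaches can therefore also inflate the error, and step 5 is a best case.

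**The case against.** The strongest objection is that the article says only robust estimation. It names no sandwich form, correction, reference distribution or significance level, and an analysis plan that is not shown could supply them. This stands as a limit on the claim: a reader might infer that the error will be about 20%, and the text does not support that without the condition of a normal-based test. It does not remove the point. The article has fixed the approach for region, and the choice of reference only decides whether the cost falls on type I error or on precision and power.

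Five further inferences are tempting and should not be drawn.

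- **That every analysis inherits these standard errors.** The four continuous scales go to multilevel growth models, and no growth model was simulated. The separate issue there is that, if region is a random level, its variance rests on 2 df.
- **That the comparison with the full AHV tenant population has only three clusters.** It may include tenants outside the three regions.
- **That joint tests of the confounders would fail.** The variance matrix does have low rank, but the confounders are adjustment variables and no joint test is planned.
- **That community-level determinants take only three values.** The article says they are measured in the surveys, and Table 1 lists personal responses such as connection to culture and community. There is no reason to drop that analysis.
- **That coach is meant as a cluster identifier for decliners too.** The text limits it to "similarity of outcomes between people receiving life coaching from the same life coach".

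It is also fair to say that the good performance of the fixed effect in steps 4 and 5 assumes no coach clustering.

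**Conclusion.** The point holds for the linear and logistic comparisons confined to the three regions, above all coached versus declined. Three regions cannot support region-clustered robust inference. With a normal-based test the type I error is about 19% analytically, and 18-28% in simulation with the finite-sample factor, against a conventional 5%. With t(2) it is about 5-10%, with intervals about 2.2 times as wide and roughly 35-45% power for an assumed 0.45 SD effect.

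The figures rest on assumed region sizes, ICC, effect size and significance level, and on reading robust estimation as a sandwich variance. Only a linear model was simulated. The ICC matters little; unequal regions and uneven uptake make the error larger.

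**What to change.** - **Region.** Replace the region part of the clustering sentence with wording such as: in comparisons confined to the three regions, region enters the model as a fixed effect (two indicator terms) and is not used as a cluster for robust standard errors.
- **Growth models.** Do the same if region would otherwise be a random level.
- **Life coach.** Handle it separately and in the coached group only, by a partially nested model with a random coach effect among coached participants, or by a small-sample-corrected variance such as CR2 with Satterthwaite degrees of freedom. State the expected number of coaches, because step 6 shows that it matters.

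The cost is about two sentences, two degrees of freedom and no new data. The downside is that conclusions apply to these three regions and do not extend to a wider population of regions.

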#### Outcome comparisons and SEWB over the period of life coaching

The final comparison compares the SEWB of life coaching participants with non-participants. The assessment of outcomes will be made by analysing a range of outcome variables reflecting the holistic nature of SEWB as defined earlier. Several aspects of the program delivery are hypothesised to bring about changes in the SEWB of life coaching participants. These include the total hours spent in life coaching, the period of life coaching, the number of and degree to which participants achieve goals and their related actions. It is anticipated that the type of goal chosen will influence which outcomes variable may change. For example, a goal to improve financial resources would likely result in a reduction in financial stress and perhaps an improvement in wellbeing but may have less impact on other outcomes such as connection to culture.

The predictor and outcome variables of interest are shown in Table 2.

**Table 2 Tab2:** Predictor and outcome variables

Predictor variables	Outcome variables
Period of life coaching (months)	Employment status
Exposure/dose of life coaching (hours)	Financial stress
Type of goal (category e.g., financial, employment)	Strengths based parenting
Number of goals (not achieved/partially achieved /achieved)	Connection to culture
Number of actions (not achieved/partially achieved/achieved)	Service use
	Health
	Wellbeing - resilience, psychological distress and mental health

Given the non-randomised design, adjusted analyses will be conducted to delineate whether any observed differential outcomes are due to coaching or could be accounted for by initial differences between the people who chose or declined to participate in life coaching. Comparisons will be adjusted for confounders specified a priori (as above) as well as baseline measure corresponding to the outcome under consideration.

For outcomes measured on a continuum (Euroqual 5D-5L, Kessler-5, Mental Health Continuum, and Aboriginal Resilience and Recovery Questionnaire) multilevel growth models [42] will be used to examine within-person change over time within individuals and communities in each region. The models will be extended to examine the effects of family contexts on the growth curves including individual, family and community level social determinants as measured in the surveys.

Exploratory analyses will be conducted to examine whether the effects of life coaching may be modified by the presence of family violence, family structure (e.g., single parent) or age of children (young vs school aged or teenagers).

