## Discussion

The MTAL study will contribute to advancement of knowledge, with the results being used to advocate for interventions of this type within the communities of interest and with funders.

A limitation of the study is that the sample of people included in the study is not representative of the general population of Aboriginal and Torres Strait Islander people. The sample does, however, reflect generally the population of tenants of community housing for which this intervention is targeted. The degree to which survey and participants reflect the population of AHV community housing tenants will be determined in the comparative analysis. Previous experience of the life coaching intervention at AHV indicate life coaching participants whose life is more stable are more able to engage in life coaching. The study will assist in identifying which populations the intervention may best be extended to through comparisons of the administrative data collected on all AHV tenants.

The COVID-19 pandemic adds a layer of complexity to rolling out this study. While peer researcher can transition from face to face to remote survey administration if the pandemic requires this, this is less desirable for life coaching. In the initial period of life coaching, face to face meetings assist with the essential task of relationship building between the tenant and the life coach. To address this need, life coaches may need to meet with the tenant initially in public spaces.

Another key implementation challenge is the anticipated turnover in peer researcher staff. Local peer researcher staff are engaged on casual contracts to administer the survey in their region when needed. Peer researchers, who are themselves tenants of AHV, are likely to experience change in their life circumstances during the course of the 18 month roll out of surveys. To manage this risk, more peer researchers will be trained than needed for the survey roll out to allow for loss to follow-up. In addition, peer researchers may be able to undertake surveys in other regions if required.

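### Coaching hours, coaching period and goals achieved are post-baseline variables read causally, so a dose or goal association with wellbeing can arise with no coaching effect

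*Protocol article*

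**What the plan says.** The section Outcome comparisons and SEWB over the period of life coaching opens with the comparison of life coaching participants and non-participants. It then adds a second line of inquiry: "Several aspects of the program delivery are hypothesised to bring about changes in the SEWB of life coaching participants". The features named are these: "These include the total hours spent in life coaching, the period of life coaching, the number of and degree to which participants achieve goals", together with the related actions.

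Table 2 in that section lists five predictors. They include "Exposure/dose of life coaching (hours"), "Number of goals (not achieved/partially achieved /achieved") and "Type of goal (category e.g., financial, employment"); the others are the months of coaching and the number of actions by achievement status. The outcomes beside them include employment status and financial stress. The text gives its own example of the link: "a goal to improve financial resources would likely result in a reduction in financial stress and perhaps an improvement in wellbeing".

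Other sections fix the timing and source of these variables:

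- **Survey and life coaching participants:** coaching is offered after the baseline survey.
- **Life coaching intervention:** contact is weekly for four weeks, then roughly fortnightly, for up to 18 months.
- **Survey:** outcomes are measured at baseline, 6 and 18 months.
- **Support plan and pulse checks:** the goal data come from the coach, as this sentence shows: "Each life coach will document information about goal category, actions to achieve goals, goal status and goal attainment date in a support plan".

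Adjustment is for the a priori confounders and the baseline value of the outcome. Its stated purpose is to deal with initial differences between people who chose coaching and people who declined it. Only the effect-modification analyses (family violence, family structure, age of children) are called exploratory.

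**The concern.** All five predictors come into being after baseline and only for coached people. How long someone stays in coaching, how many hours they receive and how many goals they reach can all depend on how their life is going during follow-up, which also drives the outcome. Adjusting for baseline values does not remove that shared cause when it changes after baseline.

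Goal attainment has a further problem. A person who achieves an employment goal will usually also be recorded as employed. The association then largely restates the outcome and says little about whether coaching produced it.

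The Discussion intends the results to support advocacy with communities and funders. A dose-response finding would be persuasive there, and as planned it could not be told apart from one that arises without any coaching effect.

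**Working it through.** **The plan's own numbers.** Under Study population (Fig. 1 text), 389 × 0.51 = 198.4, against a stated 200 surveyed (200/389 = 51.4%), and 200 × 0.73 = 146 coached. Both reproduce. The article gives no significance level, effect size, standard deviation or dropout rate, so there is no power figure to reproduce.

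**Time order.** Take 26 weeks for 6 months and 78 weeks for 18 months, coaching starting at about the baseline survey, and one contact at each scheduled point.

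- Contacts by 6 months: 4 + (26 − 4)/2 = 15.
- Contacts by 18 months: 4 + (78 − 4)/2 = 41.
- Share after the 6-month survey: (41 − 15)/41 = 63%.

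For someone coached for the full period, most of the total dose would come after the 6-month outcome it is meant to predict.

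**False-positive rate with no coaching effect.** Assumptions, none of them in the article: baseline and 18-month outcome correlate 0.6; dose (or goals achieved) correlates ρ with the part of post-baseline change not due to coaching; two-sided 5% test. The model is

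- outcome at 18 months = 0.6 × baseline + √(1 − 0.6²) × e = 0.6 × baseline + 0.8 × e
- dose = ρ × e + √(1 − ρ²) × independent noise

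The 18-month outcome is regressed on dose and baseline with robust standard errors, 1,500 runs per cell:

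| ρ | 146 coached | 100 coached | Spurious slope (SD per SD of dose) |
|---|---|---|---|
| 0 | about 6% | about 6% | 0 |
| 0.1 | 23% | 17% | 0.08 |
| 0.2 | 68% | 54% | 0.16 |
| 0.3 | 96% | 87% | 0.24 |
| 0.4 | over 99% | 99% | 0.32 |

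The slope is 0.8 × ρ, as the model implies.

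**Analytic check (Fisher z).** The test statistic is centred at atanh(ρ) × √(n − 3).

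- n = 146, ρ = 0.2: 0.2027 × √143 = 2.42, rejection 68%.
- n = 146, ρ = 0.3: 0.3095 × √143 = 3.70, rejection 96%.
- n = 102 (30% lost, an assumption: 146 × 0.7 = 102): 52% and 87%.

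**Contrast for comparison.** In null data for 200 people, with uptake unrelated to outcome, coached yes/no rejects in 4.5% to 6.3% of runs at every ρ. Hours entered as zero for uncoached people (simulated mean 30, SD 12 among the coached, also assumed) reject in 5%, 12%, 31%, 60% and 82% of runs at ρ = 0, 0.1, 0.2, 0.3 and 0.4.

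**Overlap.** Table 2 gives financial and employment as goal categories on the predictor side, and lists financial stress and employment status on the outcome side. No simulation is needed: for these pairs, predictor and outcome describe nearly the same event.

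**The case against.** The strongest reply is that the size of the bias rests entirely on an assumed correlation that the article does not supply. That is correct. At ρ = 0 the error stays near its nominal level, and if people in difficulty receive more hours the bias runs the other way.

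A reader might infer from the Discussion's remark that "life coaching participants whose life is more stable are more able to engage in life coaching" that the plan itself says improvement generates dose. It does not. Stability there can be read as a pre-existing trait, as it is under Study population. Housing stability, financial stress, employment, and health and wellbeing are all among the a priori confounders, so baseline adjustment absorbs part of that link. What remains is change after baseline, which the stated adjustment does not address.

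The hypothesis is worded as a hypothesis and confined to coached participants, which points towards a within-coached question. How the predictors enter a model, and with what lag, is ordinarily left to the analysis plan. Goal attainment dates are recorded, so goals can be time-ordered. Outcome surveys are administered by peer researchers, not by coaches. All of this stands and narrows the point. It does not remove it: the article itself fixes the predictor list and its causal reading, and does not label these analyses exploratory although it does so for others.

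A reader might also infer that coaching hours will not be recorded, because Table 1 and the support plan description do not list them. A condensed article does not support that inference.

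**Conclusion.** The point holds as a limit on what the delivery variables can show. With no coaching effect, a dose or goal association in 146 coached people would be declared significant with probability of about 6%, 23%, 68% or 96% for assumed residual correlations of 0, 0.1, 0.2 or 0.3. The direction of bias for hours and months is not known in advance. For employment and financial goals paired with the matching outcome, the overlap is close to definitional.

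Three stronger conclusions are not supported:

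- A spurious dose effect is not certain. It needs dose to track change that coaching did not cause.
- Hours and months are not themselves the outcome. The overlap concerns goals and actions achieved.
- The coached versus non-participant comparison is neither absent nor invalidated. It is missing from Table 2's predictor list but opens the section and does not use the delivery variables. Its near-nominal error rate above assumes uptake unrelated to outcome; self-selection is a separate matter.

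**What to change.** 1. In Table 2, name coached versus declined as the predictor for effect statements.
2. Label hours, period, goals and actions as exploratory or descriptive, within coached participants only.
3. If a dose analysis is kept, use hours and goals recorded up to the 6-month survey to predict the 18-month outcome, adjusted for baseline and 6-month values. This puts dose before outcome. It does not remove every shared cause, so the exploratory label stays.
4. Do not use attainment of an employment goal to predict employment status, or of a financial goal to predict financial stress.

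The change is to one table and a few sentences; design and recruitment are untouched. The cost is that people missing at 6 months drop out of the landmark analysis and that no causal dose claim can be made.
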